### Study visits

Physicians and study nurses blinded to the intervention will perform study documentation and patient assessment. Since the trial is designed as an observer and patient blinded RCT, information about the surgical procedure will not be disclosed to any assessors during the follow up examinations. There will be five study visits in total. The first visit will be preoperative after informed consent is obtained. Postoperatively, study visits will be performed at discharge, 6 weeks and 12 and 36 months. Each study visit includes collection of data on weight, blood tests, in particular, metabolic parameters such as hormonal assessment, glucose levels and lipid profile. Measurement of metabolic parameters will be conducted preoperatively and 6 weeks and 12 and 36 months postoperatively after a 12-hour fast and at 60 and 120 minutes after a standardized test meal (375 kcal). In addition, questionnaires will be also assessed (Gastrointestinal Quality of Life Index (GIQLI), Simplified Nutritional Appetite Questionnaire (SNAQ), Gastroesophageal Reflux Disease Questionnaire (GERDQ), Bariatric Analysis And Reporting Outcome System (BAROS) and the Sigstad score) at each visit. Furthermore, triglycerides (TG), total cholesterol, high-density lipoprotein (HDL), low-density lipoprotein (LDL), ghrelin, glucagon-like peptide-1 (GLP-1), peptide YY (PYY), glucose, insulin and bile acids will also be evaluated. Postoperatively additional data on morbidity (surgical and non-surgical short-term and long-term complications) and mortality will be collected.

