### Study endpoints

#### Primary endpoint

The primary endpoint is the EWL at 12 months after surgery (LRYGB or LMGB). For the EWL calculation (percent) the pre-surgical total body weight (at the patient’s hospital entry time) and postsurgical total body weight at one year postoperative is measured.

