#### Analysis of endpoints

The study results will be reported in adherence to the extension of the Consolidated Standards of Reporting Trials (CONSORT) statement from 2010 on reporting of non-inferiority randomized trials [17]. Summary statistics will be used to describe and compare patient characteristics of all suitable but non-included patients and all included patients (overall and stratified for the two treatment arms). Study endpoints will primarily be analyzed for the per protocol (PP) population. Sensitivity analysis will be conducted for the intention-to-treat (ITT) population. Thereby the ITT population includes all randomized patients in the groups to which they were randomly assigned, regardless of their adherence to the entry criteria, regardless of the treatment they actually received and regardless of subsequent withdrawal or deviation from the protocol. In the PP population all protocol violators, including anyone who switched groups or missed measurements are excluded. For each group, number of participants (denominator) included in each analysis and whether the analysis was by original assigned groups will be given. Additional sensitivity analysis will be used if, despite all efforts taken to ensure complete data collection, the number of missing data is non-negligible or could potentially bias the results and conclusions.

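### The primary per-protocol set excludes patients for missed measurements without limiting this to the endpoint analysed, so patients with both weights known can leave the 12-month EWL analysis

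*Protocol article*

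**What the plan says.** The rule is in the protocol article, Statistical analyses, under Analysis of endpoints. It sets the order of the populations: "Study endpoints will primarily be analyzed for the per protocol (PP) population", and "Sensitivity analysis will be conducted for the intention-to-treat (ITT) population". It then defines the PP set: "In the PP population all protocol violators, including anyone who switched groups or missed measurements are excluded". The same section promises to report the denominator of each analysis. It also promises extra sensitivity analysis if missing data are more than negligible or could bias the conclusions.

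The section Primary endpoint shows which data the primary analysis needs. EWL is calculated from two weights, the pre-surgical one taken at "hospital entry time) and postsurgical total body weight at one year postoperative is measured".

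The section Study visits shows how much else is scheduled. "There will be five study visits in total": one before surgery, one at discharge, and three later ones at 6 weeks, 12 months and 36 months. On their content the article says: "Each study visit includes collection of data on weight, blood tests, in particular, metabolic parameters such as hormonal assessment, glucose levels and lipid profile". Metabolic samples are taken fasting, then "at 60 and 120 minutes after a standardized test meal (375 kcal"). Patient-reported instruments come on top: "In addition, questionnaires will be also assessed", five of them being named.

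**The concern.** The exclusion rule is wider than the endpoint requires. One PP population is defined for all endpoints, and missing a measurement is enough to leave it. Two weights determine the primary outcome, while the visits also collect blood tests, timed samples after a test meal and several questionnaires. Under the rule as worded, any gap in these removes a patient whose 12-month EWL is fully known.

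Two things are at stake:

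- **Precision.** Known primary outcomes are discarded, in a trial whose dropout allowance takes it down exactly to its required number.
- **Selection.** Whether a patient gives a 120-minute sample or fills in a form is decided after randomization. Selecting the primary set on this weakens the comparability that randomization provides. Nor does it give a cleaner contrast between the operations, which is the usual reason for excluding patients who switched groups.

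The wording also allows two different primary sets from the same data, one defined by endpoint and one across the whole schedule. The conclusion depends on where one confidence limit falls relative to –10% EWL, so this choice should be fixed before the data are seen.

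**Working it through.** **Step 1. Compare the rule with the data needed.**

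| Item | Needed for 12-month EWL? | Could its absence exclude under the literal rule? |
|---|---|---|
| Weight at hospital entry | Yes | Yes |
| Weight at 12 months | Yes | Yes |
| Fasting or test-meal sample | No | Yes |
| Questionnaire | No | Yes |
| 36-month visit | No | Yes |

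Only the first two rows should decide membership of the primary set. Nothing in Analysis of endpoints, Analysis of primary endpoint or Analysis of secondary endpoints confines the rule to them.

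**Step 2. Reproduce the plan's sample size.** Inputs from Sample size under Statistical analyses: margin 10, SD 15 in both arms, one-sided 2.5%, power 80%. A true difference of 0 is assumed, because the article gives no figure.

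- n per arm = 2 × 15² × (1.960 + 0.842)² / 10² = 35.3, rounded up to 36, so 72 in total.
- 72 / 0.90 = 80.

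Both figures agree with the article.

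**Step 3. Find the reserve.**

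- Full 10% dropout: 80 × 0.10 = 8 lost, 72 left. There is no reserve above the required 72.
- The 2.5% loss at one year that the earlier Sample size section calls realistic: 80 × 0.025 = 2 lost, 78 left. The reserve is 78 − 72 = 6 patients.

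**Step 4. Illustrate the effect of further exclusions.** The article gives no rate of missed secondary measurements. I assume that a further 5% (4 patients) or 10% (8 patients) of the 80 have both weights but miss something else, split equally between arms.

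Power = Φ(10 / (15 × √(2/n)) − 1.96), with n per arm. For n = 36 this is Φ(2.828 − 1.96) = Φ(0.868) = 80.7%.

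| Starting point | Further exclusions | Patients left (per arm) | Power |
|---|---|---|---|
| 2.5% loss | none | 78 (39) | 83.7% |
| 2.5% loss | 4 | 74 (37) | 81.8% |
| 2.5% loss | 8 | 70 (35) | 79.6% |
| 10% dropout | none | 72 (36) | 80.7% |
| 10% dropout | 4 | 68 (34) | 78.5% |
| 10% dropout | 8 | 64 (32) | 76.0% |

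A calculation with the noncentral t distribution gives values about one percentage point lower (for example 79.7% at 36 per arm and 74.7% at 32) and the same pattern. If exclusion for missing data is limited to the two weights, only the rows without further exclusions apply.

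**The case against.** The strongest reply is that exclusion by endpoint was meant all along. The trial is sized for EWL at 12 months, the expected loss is stated at one year, and EWL at 36 months is a separate repeat of the analysis. The promised denominator for each analysis fits sets that vary by endpoint. Taken literally, the rule would keep the 12-month set open until the 36-month visit, which the authors are unlikely to have wanted. This reading is plausible. But a promise to report denominators does not define a population, and it is kept under either reading.

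A second reply is that a journal article need not give every detail of a PP definition. That would hold if the article were silent. It states a rule, and states it too broadly.

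A third reply is that the intention-to-treat (ITT) analysis keeps these patients, and that the conditional analysis for missing data would be triggered if gaps were common. Both stand as partial safeguards and could reveal a discrepancy. Neither is primary, so the non-inferiority conclusion would still come from the reduced set.

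Finally, the exclusion rates are assumed. That is correct, and at the loss the article calls realistic, power stays close to 80% even with a further 10% excluded.

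A reader might infer that the trial is underpowered, or that its primary result will be biased towards non-inferiority. The article supports neither. It gives no rate of missed measurements, and nothing in it indicates a difference between arms or a direction of bias. Loss of power by itself makes non-inferiority harder to show.

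**Conclusion.** The point holds as a fault in how the primary analysis set is defined. As worded, the rule can remove patients whose primary outcome is known, on grounds unrelated to that outcome and arising after randomization.

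Its size cannot be determined from the article. Under the assumed further exclusions of 5% to 10% of the 80, the loss is about 2 to 4 percentage points of power from 78 patients (83.7 − 81.8 = 1.9; 83.7 − 79.6 = 4.1) and about 2 to 5 points from 72 (80.7 − 78.5 = 2.2; 80.7 − 76.0 = 4.7). These figures rest on a true difference of 0, an SD of 15 and equal exclusions in both arms. The selection risk is real in principle but not quantified. Under an endpoint-specific rule neither effect arises from missed secondary measurements.

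This is not an objection to a PP primary analysis in a non-inferiority trial, nor to excluding patients who switched groups. It is a correction that should be made, and not a fatal defect.

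**What to change.** Add one clause to Analysis of endpoints, along these lines:

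*For the PP analysis of 12-month EWL, a missed measurement means a missing weight at hospital entry or at 12 months; for 36-month EWL, a missing weight at hospital entry or at 36 months. A missing blood sample, questionnaire or later visit is not a reason for exclusion from the PP analysis of EWL.*

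Settle this before the 12-month analysis. It adds no visit, test or patient and leaves data collection unchanged. If exclusion by endpoint was already intended, the clause only records it.

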#### Analysis of primary endpoint

The primary endpoint is the EWL at 12 months post-surgery. To examine non-inferiority of the experimental compared to standard treatment, we assess if the two-sided confidence interval of the difference between the mean EWL in the experimental treatment group and the mean EWL in the standard treatment group does not include the non-inferiority limit of –10% EWL.

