## Background

The globally growing incidence of obesity and its related comorbidities is one of the most challenging public health issues [1]. Morbid obesity reduces life expectancy, in particular among younger adults [2]. Bariatric surgery, the only effective treatment for morbidly obese patients, has shown effective long-term weight loss and significant reduction of obesity-related comorbidities and mortality in randomized controlled trials (RCT) [3–5]. The laparoscopic Roux-en-Y gastric bypass (LRYGB) is considered the gold standard among the different bariatric procedures, achieves durable long-term weight loss and improves obesity-related comorbidities [6, 7]. The laparoscopic mini gastric bypass (LMGB), first reported by Rutledge et al. [8], has recently gained popularity as a new procedure for the treatment of morbid obesity. LMGB is suggested to be a technically less demanding operation compared to LRYGB and offers comparable benefits. Several studies have been published assessing the efficacy and safety of LMGB. The first and only randomized controlled trial comparing the LRYGB to LMGB was carried out by Lee et al. in 2005 [9]. The authors observed excess weight loss (EWL) of 64.9% after LMGB and of 64.4% after one and two years, respectively. In comparison, patients with LRYGB had EWL of 58.7% and 60.0%, respectively. Excess weight (EW) is defined as the amount of weight that is in excess of the ideal body weight (IBW), which is determined as a body mass index (BMI) of 25 kg/m^2^. Therefore, EWL is the quotient of weight loss and EW. In addition, LMGB patients had fewer postoperative complications and shorter hospitalization.

Given the increasing number of bariatric procedures performed worldwide [10], the impact on weight loss, morbidity and mortality of LMGB in comparison to LRYGB needs to be further assessed in randomized controlled trials. Therefore, the aim of the current trial is to analyze the EWL and resolution of comorbidities with LMGB and LRYGB. Furthermore, the differences in hormone levels and changes in the lipid status of patients undergoing one of these two operations will be analyzed. These results have the potential to influence bariatric surgery guidelines profoundly and may bring additional insights in the pathophysiology of the intestinal tract after bariatric surgery.

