### Inclusion criteria

Patients aged 18 years or older with a BMI between 35 and 50 kg/m^2^ and eligible for bariatric surgery according to the SMOB guidelines will be enrolled.

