### Randomization

Eligible patients, who give confirmed consent, are randomly assigned to one of the two operating techniques. Randomization will be performed using sequentially numbered, sealed, opaque envelopes. Computer-generated block randomization is used to ensure an equal number of patients in each treatment group. The block size used is not available from the study protocol and is unknown to the investigator, to keep the potential for selection bias at the lowest level possible. Patients will be allocated to a study group by the operating surgeon immediately prior to the operation.

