### Statistical analyses

#### Sample size

If LMGB is non-inferior to LRYGB, 72 patients are required (36 patients per study arm) to have an 80% chance that the lower limit of the one-sided 97.5% confidence interval (equivalently a 95% two-sided confidence interval), does not include the non-inferiority limit of –10% EWL when assessed at 12 months. Given an anticipated dropout rate of 10%, the total number of patients to be included in the study is 80 (40 patients per arm). The non-inferiority limit of –10% EWL was chosen based on expert bariatric opinion. Furthermore a standard deviation of 15 was assumed in both arms according to a study from Lee et al. [9]. For further details on calculations see “Analysis of endpoints”.

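### The primary EWL comparison is valid but less precise than it could be: it names no adjustment for baseline BMI, which enters the definition of EWL and is already collected

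*Protocol article*

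**What the plan says.** In its section Analysis of primary endpoint, the protocol article assesses non-inferiority from "the two-sided confidence interval of the difference between the mean EWL in the experimental treatment group and the mean EWL" in the standard arm, checked against -10 points of EWL. No covariate is named there or elsewhere. The section Analysis of secondary endpoints repeats the same analysis at 36 months.

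The Background section says that "EWL is the quotient of weight loss and EW", where EW is the weight above a BMI of 25 kg/m². Eligible patients are those "with a BMI between 35 and 50" kg/m². On allocation, the Randomization section says that "Computer-generated block randomization is used to ensure an equal number of patients in each treatment group". It mentions no stratification by BMI and does not rule it out.

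The sample size section uses a "one-sided 97.5% confidence interval (equivalently a 95% two-sided confidence interval"), and 36 evaluable patients per arm are meant "to have an 80% chance that the lower limit" clears the margin. It also states that "The non-inferiority limit of –10% EWL was chosen based on expert bariatric opinion" and that "a standard deviation of 15 was assumed in both arms". Pre-surgical weight is recorded at hospital entry for the EWL calculation.

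**The concern.** EWL has baseline excess weight as its denominator. Across the eligible range that denominator runs from 10 to 25 BMI units, so two patients who lose the same share of their body weight can have very different EWL. Part of the spread in the primary endpoint is therefore likely to come from a quantity that is known before surgery and has nothing to do with the operation. A plain difference in means leaves this spread in the error term.

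What is at stake is precision. The trial is small, its power is only about 80%, and the margin is 10 points. Removing predictable variation would narrow the interval that decides the verdict, at almost no cost.

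**Working it through.** **1. The plan's own figure.** Inputs from the sample size section: margin 10, SD 15, one-sided alpha 0.025, power 80%, 1:1 allocation. The true difference is not stated; 0 is assumed.

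- n per arm = 2 × 15² × (1.960 + 0.842)² / 10² = 35.3, rounded up to 36. The total is 72, and 72 / 0.9 = 80. Both stated figures reproduce.
- Power at 36 per arm is 80.7% by the normal approximation and 79.7% by the noncentral t.
- Half-width of the unadjusted 95% interval = 1.96 × 15 × √(2/36) = 6.93 points.

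**2. How EWL depends on BMI.** Write %TWL for percent total weight loss. From the definition in the Background section:

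EWL = %TWL × BMI / (BMI - 25)

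| Baseline BMI | Multiplier | EWL if %TWL = 25 |
|---|---|---|
| 35 | 3.5 | 87.5 |
| 50 | 2.0 | 50.0 |

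For EWL to be unrelated to BMI, %TWL would have to be 3.5 / 2.0 = 1.75 times as high at BMI 50 as at BMI 35.

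**3. Gain as a function of the unknown correlation.** The article gives no BMI-EWL correlation (rho), so a range is shown. Residual SD = 15 × √(1 - rho²). The half-width is 1.96 × residual SD × √(2/36). Power comes from simulating both analyses (20,000 runs per row, 36 per arm, true difference 0).

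| Assumed absolute rho | Residual SD | Half-width | Power, unadjusted | Power, adjusted |
|---|---|---|---|---|
| 0 | 15.0 | 6.93 | 80.1% | 79.5% |
| 0.3 | 14.3 | 6.61 | 80.0% | 83.1% |
| 0.5 | 13.0 | 6.00 | 79.7% | 89.4% |
| 0.6 | 12.0 | 5.54 | 79.6% | 93.3% |

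With the true difference set at -10, one-sided type I error stayed near 2.5% for both analyses.

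**4. Where rho might lie, under added assumptions.** Suppose %TWL does not vary with BMI, mean EWL is 62 (between the one-year values of 58.7 and 64.9 that the Background section quotes), mean BMI is 42 to 43, and the SD of BMI is 3 to 4. Mean BMI, its SD and the constant %TWL are assumptions; the article gives none of them.

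- Slope = -25 × EWL / [BMI × (BMI - 25)]. At BMI 43 this is -25 × 62 / (43 × 18) = -2.00. At BMI 42 it is -25 × 62 / (42 × 17) = -2.17 points per BMI unit.
- R² = (slope × SD of BMI / 15)². The low end is (2.00 × 3 / 15)² = 0.16 and the high end (2.17 × 4 / 15)² = 0.34, so the absolute rho is 0.40 to 0.58.
- Residual SD is 13.7 down to 12.2. Noncentral-t power at 36 per arm is 86% to 93%.
- If the slope were half as steep, rho would be 0.20 to 0.29 and power about 81% to 83%.

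**5. Chance imbalance, same assumptions.** The SE of the difference in mean BMI is SD × √(2/36), which is 0.71 to 0.94 units. A 2-SE imbalance is 1.4 to 1.9 units and moves the unadjusted difference by 1.41 × 2.00 = 2.8 to 1.89 × 2.17 = 4.1 points. A 1-SE imbalance moves it by 1.4 to 2.0 points.

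**The case against.** The strongest reply is that nothing here is an error. The unadjusted interval has correct type I error, and the sample size was planned for exactly that analysis. This stands, and the point is put only as a gain in efficiency.

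Three further objections also stand:

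- A reader might infer that chance imbalance in BMI biases the result or threatens the verdict on top of the stated error rates. The documents do not support that. Under randomisation such imbalance is random error and is already inside the SD of 15 and the half-width of 6.93 points. A shift of 3 to 4 points needs a 2-SE imbalance, which occurs in about 5% of trials, and in about half of those against the mini bypass.
- A reader might take 86% to 93% as the expected power. It depends on a BMI spread and a constant percent weight loss that the article does not report. With a weak correlation the gain is a few points, and with none there is a loss of about half a point.
- Adjustment does not remove chance imbalance in general. It corrects for BMI alone, and only as far as the fitted form is right. The relation in step 2 is curved.

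One objection stands only in part. A condensed article may leave covariates to an analysis plan that is not shown, and the absence of BMI strata is inferred from silence. However, the primary estimator is stated, as a difference between two means. A later covariate would change that estimator, so the choice can fairly be discussed as it is written.

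**Conclusion.** The point holds as a free improvement. The planned comparison is valid and reproduces its own sample size, but it leaves in the error term a baseline variable on which the endpoint depends by construction. The direction follows from the article's definition of EWL, unless percent weight loss rises 1.75-fold across the eligible BMI range. The size is uncertain: from a loss of about 0.5 points of power at zero correlation to a gain of roughly 14 points at a correlation of 0.6 (93.3% against 79.6%). The corresponding half-width of the interval falls from 6.93 to 5.54 points. These figures assume an SD of 15, a true difference of 0 and 36 evaluable patients per arm.

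**What to change.** Before any unblinded look at outcome data, prespecify as the primary analysis an ANCOVA of 12-month EWL on treatment, with baseline BMI at hospital entry as covariate. Fix the form of the BMI term in the same text: either linear, or BMI/(BMI-25) because the relation is curved. Declare non-inferiority if the lower 95% limit of the adjusted difference lies above -10. Keep the unadjusted difference in means as a sensitivity analysis, and use the same model for EWL at 36 months.

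The cost is a change of wording and one degree of freedom. Weight at hospital entry is already recorded and BMI is needed for eligibility. The adjusted coefficient is still a mean difference in EWL points, so the margin applies unchanged, and the sample size of 80 need not move.

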#### Analysis of secondary endpoints

To investigate non-inferiority of the experimental treatment in the long term, analysis used for the primary endpoint will be repeated for EWL at 36 months post-surgery. All other endpoints will be analyzed under the assumption of superiority of the experimental treatment compared to the standard treatment. To compare the duration of surgery and the length of hospital stay between the two treatment groups, the Wilcoxon signed-rank test will be conducted (as we assume the data to be right-skewed).

The number of perioperative and postoperative complications will be analyzed by the chi-squared test or Fisher’s exact test, dependent on the observed numbers in a 2 × 2 contingency table. Additionally, we will compare the risk for complications in the two groups by calculating the risk difference with 95% confidence interval. The other secondary endpoints will be investigated using appropriate explorative methods and graphical visualization.

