### Sample size

A total of 80 patients will be randomized, with 40 patients assigned to each treatment arm. A loss of follow up at one year of 2.5% is considered realistic and it has been calculated to account for a dropout rate of 10%.

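### The lead 36-month non-inferiority analysis drops patients with no 36-month weight and makes no use of the earlier weights already collected from them

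*Protocol article*

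**What the plan says.** Three parts of the Protocol article together fix the 36-month test.

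- **Analysis of secondary endpoints:** the "analysis used for the primary endpoint will be repeated for EWL at 36 months post-surgery". It is the only endpoint besides the primary that is tested for non-inferiority.
- **Analysis of primary endpoint:** the quantity compared with the –10 limit is the "two-sided confidence interval of the difference between the mean EWL in the experimental treatment group and the mean EWL in the standard treatment group". No covariate or longitudinal model is named.
- **Analysis of endpoints:** "Study endpoints will primarily be analyzed for the per protocol (PP) population", and "In the PP population all protocol violators, including anyone who switched groups or missed measurements are excluded". The same section adds: "Sensitivity analysis will be conducted for the intention-to-treat (ITT) population". It also foresees further sensitivity work if missing data are more than negligible or might bias the conclusions. Neither provision says how a missing 36-month EWL is to be handled.

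On the data available, the Study visits section states: "Each study visit includes collection of data on weight". Post-operative visits are at discharge, 6 weeks, 12 months and 36 months. On expected loss, the Sample size section states: "A loss of follow up at one year of 2.5% is considered realistic", with 10% allowed for. No figure is given for 36 months.

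**The concern.** At 12 months, with a loss of a few per cent, a comparison of the patients who attended costs little. The same method is then carried to 36 months. By that point two more years have passed with no scheduled visit, and patients may leave at any time. Most of those lost late will already have a 12-month EWL, which plausibly predicts both the missing 36-month value and the decision to stay away. The lead analysis does not use it.

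Two things are at stake. Precision falls as patients are lost. And if poor responders leave one arm more than the other, that arm's mean among attenders is too favourable. In a non-inferiority test, such a shift in favour of LMGB raises the chance of a false claim. The endpoint is secondary, but it is listed first among the secondary endpoints, and the abstract presents the three-year follow-up as the trial's contribution.

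**Working it through.** **Inputs from the Protocol article:** 40 patients per arm, SD 15, margin –10, one-sided 2.5%, 80% power, implied true difference 0.

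**Assumptions, because the article gives no figure:** SD 15 also holds at 36 months; the correlation ρ of 12- and 36-month EWL is 0.7 (range 0.5 to 0.8); a share f = 10%, 20% or 30% is lost after month 12; everyone has a 12-month weight; there are no other per-protocol exclusions.

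**Step 1: the plan's own figure.** n per arm = 2 × (1.960 + 0.842)² × 15² / 10² = 35.3, rounded up to 36, so 72 in total; 72 / 0.90 = 80. Both stated numbers reproduce and are not in dispute. They are set for 12 months.

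**Step 2: precision under random loss.** Attender means use 40(1 – f) patients per arm. A likelihood estimate that also uses the 12-month EWL has variance (1 – ρ²f) relative to this, so the effective n is 40(1 – f) / (1 – ρ²f). For f = 20%: 32 / (1 – 0.49 × 0.20) = 32 / 0.902 = 35.5.

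| Loss f | Attenders per arm | Effective n, joint | Power, normal formula | Power, simulated t intervals |
|---|---|---|---|---|
| 10% | 36 | 37.9 | 80.7% v 82.6% | about 80% v 81% |
| 20% | 32 | 35.5 | 76.0% v 80.2% | about 75% v 79% |
| 30% | 28 | 32.8 | 70.3% v 77.1% | about 70% v 76% |

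In each pair the attender means come first and the joint model second. The simulated column is slightly lower because it uses t intervals and an estimated slope; a repeat with 40,000 runs agreed within about one percentage point. Across ρ = 0.5 to 0.8 the gain by the normal formula is 1.0 to 2.5 points at 10% loss and 2.1 to 5.5 points at 20%. At f = 0 it is zero.

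**Step 3: selective loss in one arm.** Set the true difference at –10. Let LMGB loss depend on low 12-month EWL (log-odds 1 per SD) and let LRYGB loss be random. The simulated shift in the attender difference is about 0.9, 1.8 and 2.6 points at 10%, 20% and 30% loss. The resulting one-sided error can be checked by hand as 1 – Φ(1.96 – shift / SE), with SE = 15 × √(2 / attenders per arm):

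- 10%: SE = 3.54; 1.96 – 0.9/3.54 = 1.71; error about 4%.
- 20%: SE = 3.75; 1.96 – 1.8/3.75 = 1.48; error about 7%.
- 30%: SE = 4.01; 1.96 – 2.6/4.01 = 1.31; error about 10%.

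The joint estimate is unbiased to within 0.1 point in these scenarios, and its error stays near 2.5%. With half the selection strength, the attender error is roughly 4.5% to 5.5% at 20% to 30% loss.

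**Step 4: the bounds.** In the extreme case the worst 20% by 12-month EWL all leave one arm. The shift is then 15 × φ(z₀.₂₀) / 0.80 × ρ = 5.25ρ, which is 2.6 to 4.2 points for ρ = 0.5 to 0.8. At the other end, with equal selection in both arms, the shift is essentially zero and the error stays near 2.5%.

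**The case against.** The strongest objection is that changing only the 36-month estimator would achieve nothing in the lead analysis. The per-protocol rule has already removed patients without the 36-month weight. On the complete data that remain, a mixed model with arm-by-visit terms and unstructured covariance returns the same 36-month difference as the raw means. This stands, and it is why the fix has to change the analysis-set rule as well.

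A reader might infer that the plan looks only at attenders. The documents do not support that: the article plans an intention-to-treat sensitivity analysis of all randomized patients and conditional further analyses. These provisions deserve credit. But a difference in means in the intention-to-treat set still needs a value for each missing EWL, and neither provision touches the lead result. Leaving the details of a sensitivity analysis to the full protocol or SAP is normal. The point here is the lead method and lead population, which the article does fix.

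A reader might also infer that the 36-month result will be biased. The documents do not show that either. The loss, the correlation and the selection strength are all assumed, and the larger error rates need selection confined to the LMGB arm. Blinding of patients and of staff outside the operating team makes such asymmetry harder to presume, though it does not exclude it.

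Finally, a difference in means is a legitimate analysis, and the sample size makes no power claim at 36 months. Both are true. They limit the weight of the point without removing it.

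**Conclusion.** The point holds as a cheap improvement. As written, the lead 36-month analysis discards patients who have 6-week and 12-month weights but no 36-month weight. At the only dropout allowance in the article, 10%, the power cost is one or two points; at 20% to 30% random loss it is about four to six points. Bias is the larger risk: about 1 to 3 points against a 10-point margin, with error of about 4% to 10% instead of 2.5%. That risk exists only if loss depends on response and does so differently by arm. All of these sizes assume ρ = 0.7, SD 15 at 36 months, and loss that depends only on observed 12-month EWL. The primary 12-month test and its sample size are unaffected.

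**What to change.** 1. **Analysis of endpoints:** state that, for the 36-month EWL analysis, a missing weight alone does not remove a patient from the per-protocol set. Patients who switched groups and other protocol violators stay excluded.
2. **Analysis of secondary endpoints:** replace the repeated difference in means by a linear mixed model for EWL at 6 weeks, 12 months and 36 months, with arm, visit, arm-by-visit and an unstructured covariance. Fit it in both the per-protocol and intention-to-treat sets. Read non-inferiority from the 95% interval for the arm difference at 36 months against –10. Earlier EWL enters as a joint outcome, not as a covariate: it is measured after randomization, and adjusting for it would remove part of the treatment effect.
3. Keep the completer difference in means as a supportive analysis.

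The cost is a change of wording and slightly more programming, with no new patients or measurements. The model relies on loss being explained by the observed weights. Loss driven by later, unobserved regain would still bias it, so a sensitivity analysis for that case should be added.
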